## Background

According to the World Health Organization, more than 1.4 billion adults were overweight and more than half a billion were obese worldwide in 2008, and the prevalence of obesity nearly doubled between 1980 and 2008 [1]. According to World Health Organization, in the Americas including the United States and non-continental countries, 61 % of adults are overweight or obese in 2014 [2]. In Latin America, nearly a quarter of the population is obese, and the prevalence has increased to a greater magnitude in Mexico, Argentina, and Chile. A recent review estimated that 20–25 % of the children and adolescents (0–18 years) of Latin American are overweight or obese [3]. Time trends suggest that these figures might rise further and by 2030 up to 81.9 % of the Latin American and the Caribbean adult population could be either overweight or obese [4].

These rapid epidemiological changes in the majority of developing countries over the last decades have occurred in the framework of the so-called nutritional transition. The concept of the nutritional transition includes a shift in dietary intake and energy expenditure both of which are influenced by ongoing interactions between economic, demographic, environmental, psychosocial and cultural factors and are occurring simultaneously in society [5]. Latin American countries are experiencing different stages of the nutrition transition, although the prevalence of undernutrition is declining at different rates, and the prevalence of overweight is dramatically increasing [6].

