### Analysis plan

The primary outcome of interest will be to describe the distributions of overweight and obesity, and energy intake and expenditure intake across the countries and regions of the study. A secondary objective of the study will be to identify the individual characteristics associated with the two main outcomes of interest (obesity and energy intake/expenditure) and to test whether these associations vary across the different regions by applying the statistical methodologies described below. These individual characteristics of interest will include, but are not be limited to, education, marital status, age, sex and individual income. The results of the three main outcomes will also be presented after stratification for each of the individual characteristics.

Initially, basic statistical models will be applied to analyze the aggregated results for all the individuals in the multicenter study to identify the individual characteristics (independent of area of residence) associated with each of the outcomes, with the inclusion of all the projected 9000 individuals. Separate individual models for each of the countries will also be performed.

We will also test the presence of statistically significant differences between regions of residence and countries by adjusting multilevel models (also known as hierarquical linear models), where the individual results will be included as the first level of the model and the region of residence as the second level of the model. Overweight and obesity will be analyzed separately as dichotomous dependent variables (vs. normal weight) by adjusting logistic multilevel models, while energy intake and expenditure will be treated as continuous dependent variables and multilevel linear models will be adjusted. We will test for a statistical difference of the dependent variables according to region of residence (a two-level model) and also by including the country of residence as the third level of the previous multilevel models. Statistical difference between the regions and the countries will be tested by analyzing the area-level variance (between-group variation) of each multilevel model.

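### The multilevel tests for region and country differences in obesity compare obese with normal weight only, so they test the obese-to-normal odds and not obesity prevalence

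*Protocol article*

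**What the plan says.** All of this stands in the Analysis plan section of the protocol article.

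- The primary outcome is descriptive: "to describe the distributions of overweight and obesity, and energy intake and expenditure intake across the countries and regions of the study".
- The pooled basic models for individual characteristics come next, "with the inclusion of all the projected 9000 individuals".
- A separate paragraph then adds inference on areas: "We will also test the presence of statistically significant differences between regions of residence and countries by adjusting multilevel models". Region is the second level, and country is added as a third.
- The outcome coding for these multilevel models is fixed there: "Overweight and obesity will be analyzed separately as dichotomous dependent variables (vs. normal weight) by adjusting logistic multilevel models".
- The decision rule is: "Statistical difference between the regions and the countries will be tested by analyzing the area-level variance (between-group variation) of each multilevel model".

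The section names no model of obese against all non-obese participants, and no multinomial or ordinal model of weight class.

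**The concern.** The second study aim in the Background is to measure how overweight, diet and activity vary by region and other factors, and the primary outcome is the distribution of overweight and obesity across areas. A reader will take the area test for obesity as a test of whether obesity is more common in some areas than in others.

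With normal weight as the sole comparator, the obesity model sees only obese and normal-weight people. Its area variance rises whenever overweight displaces normal weight in some areas more than in others, whatever happens to obesity. The Background describes the countries as being at different stages of the nutrition transition, so unequal overweight shares are part of the study's own premise. At stake is a conclusion about geographic differences in obesity that answers a different question from the prevalence table it accompanies.

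**Working it through.** **Inputs from the article.** Table 2 gives 1,100 participants each for Peru and Venezuela and 790 to 2,000 across the eight countries. Sampling procedures gives a design effect of 1.75. For orientation, the Background says "In Latin America, nearly a quarter of the population is obese" and "61 % of adults are overweight or obese in 2014"; the second figure covers the whole Americas including the United States. The article gives no figure for the obesity model itself, so there is none to reproduce.

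**Assumed inputs.** The weight-class shares by country are not in the article. Those below are illustrations.

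**Formulas.** For two countries A and B with equal obesity prevalence:

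- OR = (obese_B / normal_B) / (obese_A / normal_A) = normal_A / normal_B
- SE(log OR) = √(1/obese_A + 1/normal_A + 1/obese_B + 1/normal_B), using expected counts at n = 1,100
- z = log OR / SE; with the design effect, z / √1.75

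**Step 1: equal obesity, unequal overweight.** Shares are normal/overweight/obese/underweight in %.

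| Overweight gap | Country A | Country B | OR | z | z with design effect |
|---|---|---|---|---|---|
| 15 points | 50/25/25/0 | 35/40/25/0 | 1.43 | 3.30 | 2.49 |
| 10 points | 43/30/24/3 | 33/40/24/3 | 1.30 | 2.37 | 1.79 |
| 6 points | 42/33/25/0 | 36/39/25/0 | 1.17 | 1.41 | 1.07 |
| 5 points | 40/33/24/3 | 35/38/24/3 | 1.14 | 1.20 | 0.91 |
| 2 points | 38/35/24/3 | 36/37/24/3 | 1.06 | 0.48 | 0.37 |

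First row in full: counts are 550 normal and 275 obese against 385 normal and 275 obese. Log OR = ln(550/385) = 0.357; SE = √(1/275 + 1/550 + 1/275 + 1/385) = 0.108; z = 3.30; 3.30/√1.75 = 2.49.

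In the 10-point row the modelled share, obese/(obese + normal), is 24/67 = 35.8 % against 24/57 = 42.1 %. The chance of p < 0.05 is 66 %, or 44 % with the design effect. In the 2-point row it is 7 % and 6 %. In every row the odds ratio for obese vs not obese is 1.00.

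**Step 2: eight countries.** The planned test is on a variance component, not on pairs. As a stand-in, 4,000 simulated surveys at the Table 2 sizes were tested with a 7-df heterogeneity chi-square at 0.05. Obesity was 24 % and underweight 3 % in every country, with overweight evenly spread over a range.

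| Overweight range | Obese vs normal: rejected | Same, design effect 1.75 |
|---|---|---|
| 35 % everywhere | 5 % | 5 % |
| 33–37 % | 12 % | 9 % |
| 32–38 % | 24 % | 15 % |
| 30–40 % | 64 % | 38 % |

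With obese vs not obese, the rejection rate was 4.6 % to 5.5 % throughout.

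**Step 3: the reverse.** Take normal/overweight/obese/underweight of 32/45/20/3 and 41.6/29.4/26/3. The modelled odds are 20/32 = 0.625 and 26/41.6 = 0.625. A 6-point difference in obesity is invisible to the model.

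**Step 4: participants lost.** Taking nearly a quarter as 24 to 25 %, the Background figures imply that 61 − 25 = 36 % to 61 − 24 = 37 % are overweight but not obese. These participants leave the obesity model. In the simulations, with 3 % underweight also lost, about 38 % left.

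**The case against.** The strongest defence is that separate contrasts with normal weight are a recognised choice, close to a multinomial model. They keep the intermediate class out of the reference group and suit the secondary objective on individual correlates. In the Step 1 examples the weight distributions really do differ, so a non-null obese-to-normal contrast is not false; only reading it as a difference in prevalence is. This stands, and it is why the contrasts should be kept for correlates. It does not help where the article uses the same models to test area differences.

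Four stronger readings are tempting, and the article does not support them.

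- **That the primary outcome is compromised.** It is descriptive and does not use this coding. Prevalences by country and region are still reported.
- **That the plan contradicts its promise to include all 9000.** That phrase belongs to the basic models, in the paragraph before the multilevel ones.
- **That a particular pair of countries would be declared different.** The planned rule looks at area-level variance, so it would say only that areas differ overall. The pairwise z values show the mechanism and its scale, not the planned test.
- **That leaving open where underweight belongs, or whether overweight includes obesity, is itself a fault.** An article may leave such coding to the full protocol or analysis plan. If overweight includes obesity, the overweight model loses only the underweight, but the obesity model still loses everyone who is overweight and not obese.

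It is also fair to say that the size is unknown. With modest spread in overweight the distortion is small.

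**Conclusion.** The point holds in a limited form. As written, the region and country tests for obesity concern the obese-to-normal odds. They can signal differences where obesity prevalence is equal and miss differences where it is not. The distortion is material if overweight differs between areas by about 10 points or more (OR about 1.3 to 1.4 for two countries of 1,100). It is weak at 5 to 6 points (OR 1.14 to 1.17, not significant pairwise) and negligible at 2 points. With the design effect applied, even the 10-point pair falls short of significance (z 1.79), although the eight-country stand-in still rejects in 38 % of runs when overweight spans 30–40 %.

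These sizes rest on assumed weight-class shares, on a design effect applied as a simple reduction in sample size, and on a chi-square in place of the variance test. The mechanism does not depend on those assumptions; it follows from the stated coding.

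**What to change.** For the region and country variance tests, define the outcomes on everyone with a valid BMI: obese vs not obese, and overweight-or-obese vs neither, with underweight in the comparator. Alternatively, fit one multinomial multilevel model of weight class and report predicted prevalences by area. Keep the contrasts with normal weight for the analysis of individual correlates, and state that they are not to be read as differences in prevalence.

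The cost is a change of wording and a recoding of an outcome already measured; no new data are needed. The small downside is that the comparator for obesity becomes more mixed, so associations with individual characteristics will be somewhat weaker in the full-denominator model. The retained normal-weight contrasts cover that.

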### Anthropometric measurements

In each country, the anthropometric measurements of body weight, height and waist, hip and neck circumferences were collected according to standardized procedures. The participants were measured after all heavy clothing, pocket items and shoes and socks are removed. Body weight was measured with a calibrated electronic scale up to 200 kg with an accuracy of 0.1 kg. Height was measured with a portable stadiometer up to 205 cm with an accuracy of 0.1 cm. The measurements were taken during inspiration, with the base of the stadiometer lightly touching the upper reaches of the head and with the participant’s head in the Frankfort Plane [34]. The circumferences were measured with an inelastic tape to the nearest 0.1 cm. Waist circumference was measured according to World Health Organization recommendations, i.e., with the participants standing, after a regular expiration, to the nearest cm, midway between the lowest rib and the iliac crest [35]. Hip circumference was recorded at the level of the greatest posterior protuberance of the buttocks, with the tape held horizontally flat without pressing the soft tissues. Neck circumference was measured at the point just below the larynx (thyroid cartilage) and perpendicular to the long axis of the neck (with the tape line in the front of the neck at the same height as the tape line at the back of the neck) [36].

The interviewers were trained to collect all measurements by certified nutritionists/dietitians who will simultaneously operate as supervisors of the fieldwork. Each measurement was repeated twice to ensure accuracy, and the average used for the analyses. If the two readings differ by more than the previously established set point (0.1 kg for weight, 0.5 cm for height, 0.5 cm for neck circumferences, and 1 cm for waist and hip circumferences), then a third measurement was taken. All three measurements were recorded, and the outlier excluded during the data cleaning process.

The body mass index (BMI; weight (kg)/height (m^2^)) and waist-to-hip ratio were calculated. The absolute values of each circumference measurement were compared to predefined cutoff points according to age and gender.

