### Personnel training

To validate and harmonize the methodologies, a general training meeting was held with all of the PIs and the ELANS coordination center. The scientists in charge of every research tool attended the meeting. At the end of this training, national teams were placed in charge of translating the field protocol into the local language and submitting the protocol to the local ethical review boards of the participating institutions. Each study site was also responsible for training their personnel for the pilot and field studies. The interviewers were required to have completed at secondary education. Training lasted from 7 to 10 days at each site.

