### Quality control strategies

Quality control strategies were applied using a framework that comprehensively considered each phase of the study. To ensure accurate, standard and consistent measurements throughout this multicenter study, a variety of procedures were used and are described in Table 3. One the key aspects of the quality control was the development of the manual of operations to keep same methodology and procedures among all sites. The crucial roles of the PIs were focused on supervising of pilot test and fieldwork, identify and decide on the necessary amendments to the study protocol, coordinate all the trainings, ensuring accuracy of data entry and identifying inconsistencies and standardized procedures across the sites. The coordinating center audited the complete procedures for the countries.

**Table 3 Tab3:** Quality assurance strategies

Levels of quality control	Phases			
	Design and planning	Pilot testing	Data collection	Data analysis
Coordinating center	•Critical review of protocols •Harmonization of manual of operations for eight study sites •Coordination of timelines and activities	•Smoothness and feasibility of field operations assessed	•Monitoring field activities	•Audit and evaluate validity of findings prior to publication •Internal peer reviews prior to publication
Principal Investigators	•Review of design and planning of the study •Regular meetings with coordinating center	•Audit after completion of the pilot	•Supervising and ensuring accuracy of data entry	•Validity checks •Results review
Field Personnel	•Extensive training over a period of 7 to 10 days-theory and practical-by the study managers	•Evaluated all field and documenting difficulties	•Field coordinator will assure that procedures for data collections and quality control are followed •Additional training when necessary	
Survey Questionnaires	•Peer-reviewed •Validated •Translated to local languages	•Consistency in small pilot study will be established	•Regular checks done to assess completeness	•Incomplete questionnaires identified and discarded
Measuring Equipment	•Standardization of equipment and measurements •Acquired by each country •Development of anthropometric procedures manual	•Evaluation of calibration techniques, acceptability of use in field	•Regular calibration of equipment; faulty equipment replaced when required	

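### The area-level variance test of regional and country differences has no interviewer term, so differences between interviewers can be read as geography

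*Protocol article*

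**What the plan says.** The Analysis plan describes multilevel models with the individual at level one and region of residence at level two, then the same models with country as a third level. Overweight and obesity are fitted with logistic models, energy intake and expenditure with linear ones. The inference is stated: "Statistical difference between the regions and the countries will be tested by analyzing the area-level variance (between-group variation) of each multilevel model". No interviewer, city or census-tract level is named.

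Other sections show how the outcomes arise:

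- Dietary assessment: intake comes from 24-hour recalls conducted by the Multiple Pass Method.
- Anthropometric measurements: "The interviewers were trained to collect all measurements by certified nutritionists/dietitians".
- Personnel training: "Each study site was also responsible for training their personnel for the pilot and field studies". Also: "Training lasted from 7 to 10 days at each site".
- Quality control strategies, Table 3: measuring equipment is standardized but "Acquired by each country".

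The same sections list safeguards: a common training meeting for principal investigators, a shared manual of operations, supervision, calibration, duplicate readings and audit. The Discussion names the country-specific socioeconomic questionnaires as a threat to cross-country comparison. It does not mention interviewer or site measurement differences.

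**The concern.** An interviewer who probes a recall less thoroughly, or has a constant habit in measuring, shifts the values of all of his or her respondents in the same direction. Duplicate readings reduce random error within one operator but leave such a constant shift in place. Site-based training implies that each interviewer belongs to one country, so these shifts do not average out evenly over the map. A model without an interviewer level has nowhere to put this variance except the levels it does have, and two of those, region and country, are the ones tested.

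Comparison between countries and regions is a stated purpose of the study. If the test is inflated, a finding that regions or countries differ in energy intake or obesity may partly reflect who did the measuring.

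**Working it through.** The article states no figure for this test, so there is none to reproduce.

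**Inputs.** From the article: 9,000 projected participants, 8 countries, and the three model levels. Assumed, because the article does not give them: 40 regions (5 per country) of equal size, 9,000/40 = 225 people each; *m* interviewers per region or *J* per country with equal workloads; interviewer ICC of 0.005 to 0.02; a continuous outcome; no true geographic difference.

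**Case 1: each interviewer stays in one region; two-level region test.**

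Actual variance of a region mean: (1 − ICC)/225 + ICC/*m*. Variance the test allows for: (1 − ICC)/225.

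Ratio = 1 + 225 × ICC / [*m*(1 − ICC)]. For ICC 0.01 and *m* = 5: 1 + 2.25/4.95 = 1.45.

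The 5 % critical value of F(39, 8960) is 1.40. Rejection probability = P(F > 1.40/ratio).

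| ICC | *m* | Ratio | Rejection | Spurious share of variance (ICC/*m*) |
|---|---|---|---|---|
| 0.005 | 10 | 1.11 | 13 % | 0.05 % |
| 0.005 | 5 | 1.23 | 25 % | 0.10 % |
| 0.01 | 10 | 1.23 | 25 % | 0.10 % |
| 0.01 | 5 | 1.45 | 54 % | 0.20 % |
| 0.02 | 10 | 1.46 | 54 % | 0.20 % |
| 0.02 | 5 | 1.92 | 89 % | 0.40 % |

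**Case 1, three-level country test.** Region stays in the model. If a region mean has variance *v* (interviewer part included), a country mean over 5 regions has variance *v*/5, which is what the region level already implies. The ratio is 1 and the country test stays near 5 %.

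**Case 2: each interviewer's work is spread evenly over the 5 regions of one country; three-level country test.** Interviewer effects now cancel between regions of the same country but remain in the country mean (1,125 people).

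Ratio = 1 + 1125 × ICC / [*J*(1 − ICC)]. At ICC 0.01:

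- *J* = 20: 1 + 11.25/19.8 = 1.57
- *J* = 40: 1 + 11.25/39.6 = 1.28

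The critical value of F(7, 32) is 2.31, so rejection is about 21 % (*J* = 20) and 12 % (*J* = 40). The region-within-country test stays near 5 %.

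**Effect of an interviewer term.** In a separate simulation of balanced nested designs (20,000 draws per scenario), 40 areas with 4 interviewers each gave rejection of 31 %, 65 % and 94 % without the term at ICC 0.005, 0.01 and 0.02. With the area mean square compared against interviewers within area, all nested scenarios returned to 4.8-5.4 %.

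**What the term cannot do.** With 8 countries, 20 interviewers per country, ICC 0.01 and the term present, a shift shared by all interviewers of a country and carrying 0.2 %, 0.5 % or 1 % of the variance still led to rejection in 55 %, 87 % and 97 % of draws.

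**The case against.** Several objections have force.

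- **Nesting in regions is not documented.** A reader might infer that interviewers worked in one region each, and that region and country tests are therefore both inflated. The article does not describe assignment, and the working shows that confined interviewers leave the three-level country test near 5 %. What stands is narrower: under either of the two assignments examined, one of the stated tests is inflated.
- **The size is assumed.** Number of regions, interviewer counts and ICC are all absent, and the results run from 12 % to 89 %. The F calculation is for a continuous outcome; for the logistic models of overweight and obesity the mechanism carries over, but these percentages need not.
- **Safeguards exist.** A reader might conclude that operator differences will be reported as geographic ones. The text supports only a risk, since a common manual, investigator training, supervision, calibration and audit should all reduce operator variance. No inter-observer figure shows that it becomes negligible, and an ICC of 0.005 already matters.
- **The primary aim is descriptive.** This is true, and the false variance is a fraction of one percent, so the described distributions are little affected. The planned significance tests are affected.
- **A further random term could be left to a full analysis plan.** That would answer a complaint about silence. Here the article itself fixes the levels and the test.
- **An interviewer term may absorb real local variation** if workloads followed census tracts. This stands and is carried into the fix.

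The standard errors clustered by region and country belong to the structural equation models and do not address this test.

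**Conclusion.** The point holds as a conditional defect of a stated test. With only individual, region and country levels, the area-level variance cannot distinguish geographic differences from differences between interviewers.

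Which test suffers depends on an assignment that the article does not report: the region test if interviewers stayed within a region, the country test if they ranged over a country. The percentages rest on the assumptions listed above and illustrate sensitivity; they do not predict what this study will find. If the interviewer ICC is zero, the test keeps its 5 % level.

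The damage is to the significance test, with little effect on the estimated amount of geographic variation. Country-wide differences in training or equipment are a separate confounding that no model term can resolve.

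**What to change.** - The sponsor should confirm whether interviewer identity was recorded for each participant; the article does not say.
- If it was, add interviewer as a random effect in the multilevel models for energy intake and for overweight/obesity: below region if each interviewer worked in one region, crossed with region if not. Test region and country variance with that term present.
- If it was not, use the sampling point (census tract) as the intermediate level. This is a partial remedy, because an interviewer who covered several tracts still contributes variance above the tract.
- Report how interviewers were assigned to regions and the estimated interviewer variance, with the caution that it may include local area variation where workloads followed tracts.
- State as a limitation that a training or equipment difference shared by a whole country cannot be separated from country.

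The cost is one extra random term per model, a short table and a sentence of limitation. Region and country differences will be significant less often, and where workloads follow tracts some of that loss may be real local variation. Since fieldwork is described as ending, the analysis is where this can still be addressed.

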Studies that combine nutrition and physical activity assessment in representative samples of Latin American countries are lacking. In this direction, the Latin American Study of Nutrition and Health/*Estudio Latinoamericano de Nutrición y Salud* (ELANS), which is randomized cross-sectional multicenter investigation of the nutritional and physical activity statuses of adolescents and adults in eight Latin American countries, was designed. The study aims to (1) provide up-to-date reliable and comparable data of dietary intake, physical activity, and its association with anthropometric profile among representative urban populations of eight Latin American countries; (2) measure variation in overweight, dietary intake and physical activity by region, cultural background, socioeconomic status, age and gender; (3) add new scientific-based evidence to describe the interplay among energy intake, energy expenditure, and anthropometric measurements. Our overarching hypothesis is that the relationships between dietary and physical activity profiles will differ across countries and across different environmental settings.

Up to now, there is no Latin American study using a central standard methodology across a group of participating countries. Previous multicenter studies [23–26] were important references to determine the rationale and design of ELANS.

The purpose of this report is to describe the design and methodology of the ELANS. The study is currently ending the fieldwork data collection.

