### Overall design and methods

The ELANS is a household-based multi-national cross-sectional survey that was conducted over a period of one year in eight Latin American countries (i.e., Argentina, Brazil, Chile, Colombia, Costa Rica, Ecuador, Perú, and Venezuela; Fig. 1) that represent approximately 60 % of the total countries of Latin America. All of the study sites are academy (universities and other academic institutions)-based and adhered to a common study protocol for interviewer training, implementation of fieldwork, data collection and management, and quality control procedures that will be simultaneously performed.

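### The plan promises to test whether associations vary across regions, but the only formal between-area test it describes addresses outcome levels

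*Protocol article*

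**What the plan says.** Two statements in the protocol article concern associations.

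- Background: "Our overarching hypothesis is that the relationships between dietary and physical activity profiles will differ across countries and across different environmental settings".
- Analysis plan, secondary objective: after identifying individual characteristics associated with obesity and with energy intake or expenditure, the aim is "to test whether these associations vary across the different regions by applying the statistical methodologies described below". Education, marital status, age, sex and income are the listed characteristics, and the list is open-ended.

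The methods that follow in the Analysis plan are:

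- pooled models for all participants, and models fitted country by country;
- multilevel models, logistic for overweight and obesity and linear for energy. Their between-area test is introduced as "We will test for a statistical difference of the dependent variables according to region of residence (a two-level model", and then extended "by including the country of residence as the third level of the previous multilevel models";
- the criterion for that test: "Statistical difference between the regions and the countries will be tested by analyzing the area-level variance (between-group variation) of each multilevel model";
- structural equation models, with clustered standard errors to allow for dependence within regions and countries.

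The design section gives the number of countries: the survey was "conducted over a period of one year in eight Latin American countries".

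**The concern.** Whether average intake or obesity prevalence differs between places is one question. Whether the effect of, say, education or activity differs between places is another. The secondary objective and the Background hypothesis both ask the second, and the objective points to the methods that follow for its test. The only between-area test those methods spell out answers the first.

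An analyst who follows the text would therefore report a between-area variance and have no stated test for the secondary objective. Real differences in associations could go untested. A significant area variance could also be mistaken for evidence on associations when only the means differ. Cross-country comparison is the main value the article claims for the study, so the gap matters even though the primary outcome is descriptive.

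**Working it through.** **1. What each quantity measures.** For person i in area j, with a centred characteristic x:

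y_ij = (b0 + u0_j) + (b1 + u1_j) x_ij + e_ij

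- The area-level variance of the outcome is Var(u0). It is zero when areas share the same adjusted mean.
- Variation of the association is Var(u1). It is zero when areas share the same slope.

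Either can be zero while the other is large. With an uncentred x, slope differences can leak into the intercept variance, but that still does not make it a test of slopes.

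**2. Promise against method.**

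| Stated aim | Quantity needed | What the Analysis plan states |
|---|---|---|
| Describe outcomes across countries and regions (primary) | outcome levels, Var(u0) | area-level variance: fits |
| Associations vary across regions (secondary) | slope variation by region | no term stated |
| Diet and activity relationships differ across countries and settings (Background) | slope variation by country and setting | country-by-country models, with no comparison of coefficients stated |

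The clustered standard errors in the structural equation models change precision. They do not test whether a path differs between places.

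**3. The plan's own figures.** The article's sample-size figures are margins of error for a proportion. The largest, for Costa Rica, reproduces as 1.96 × sqrt(0.25/790) = 3.49%. No figure concerns heterogeneity of associations, so there is none to reproduce on this point.

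**4. Size of the mismatch, by simulation.**

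- From Table 2: country sizes 1200, 2000, 870, 1230, 790, 800, 1100 and 1100, total 9090.
- Assumed: x and the residual are standard normal; mean slope 0.2; between-country SDs as in the table below; simple random sampling within country; 2000 replicates; alpha 5%.
- Tests: fixed-effect F-tests on 8 − 1 = 7 numerator df, as stand-ins for the variance test (levels) and a slope-heterogeneity test.

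| SD of country means | SD of country slopes | Levels test rejects | Slope test rejects |
|---|---|---|---|
| 0 | 0 | 4.8% | 5.4% |
| 0 | 0.05 | 4.0% | 80.2% |
| 0 | 0.10 | 4.6% | 99.1% |
| 0.10 | 0 | 99.0% | 5.8% |
| 0.10 | 0.10 | 99.1% | 99.3% |

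Simulation error at 5% is about sqrt(0.05 × 0.95/2000) = 0.5 percentage points. When only slopes differ, the levels test rejects at about its nominal rate. When only means differ, it rejects almost always. The power figures ignore clustering. The article's design effect of 1.75 would cut the effective total to about 9090/1.75 = 5194 and lower them, but the contrast between the two columns comes from step 1.

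**5. Secondary: precision of a variance from eight countries.** Ignoring within-country error, the 95% interval for the country variance on 7 df is the estimate times 7/chi-square quantile:

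- lower: 7/16.01 = 0.44;
- upper: 7/1.69 = 4.14.

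On the SD scale that is 0.66 to 2.04 times the estimate. The variance can be estimated, but imprecisely.

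**The case against.** **The article leaves model terms to the analysis plan.** Random slopes and interactions are details that an article often omits, and their absence here does not show that none is intended. That stands as a caution: the correct word is not stated, rather than not planned. But the article does not leave this test open. It says that the methods it goes on to describe will deliver it, and those methods address something else.

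**The variance could include slope variances.** In principle it could. The sentence just before restricts the test to the dependent variables, and no random coefficient is mentioned.

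**The country-by-country models suffice.** They do show country-specific associations, and eight independent coefficients with standard errors could support a heterogeneity test. No such comparison is stated, and the models are by country while the secondary objective is by region.

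**The variance test suits the primary aim.** This stands fully. It is a relevant quantity for comparing outcome levels and should be kept.

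Four stronger readings are tempting but not supported:

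- *The Background hypothesis would be accepted or rejected on the area variance.* No sentence says so.
- *The Background hypothesis and the secondary objective are one claim.* The first concerns diet and activity relationships across countries and settings. The second concerns individual characteristics across regions.
- *With eight countries the variance could never reach significance.* That depends on a particular estimate-over-standard-error test, and the article names no test statistic. A likelihood-ratio test has no such ceiling.
- *Country must be a fixed effect because the countries were hand-picked.* The article does not say how they were selected, and fixed or random country is largely a modelling choice.

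**Conclusion.** The concern holds in a limited form. The stated between-area test addresses outcome levels, while the secondary objective and the Background hypothesis concern associations; as written, neither has a formal test. The conclusion rests on the article's wording and on the algebra in step 1. The simulated rates only illustrate its size, under assumed effects and simple random sampling.

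The imprecision from having eight countries is a side point. It does not apply to the two-level region test, for which the article gives no number of regions.

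This should be fixed, but it is not critical: the primary outcome is descriptive, and sampling and data collection are unaffected.

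**What to change.** 1. Keep the area-level variance test and state that it concerns differences in outcome levels.
2. For the secondary objective, add region-level random slopes for the named characteristics. Test each slope variance with a likelihood-ratio test whose reference distribution allows for the null lying on the boundary.
3. For the Background hypothesis, name the diet and physical activity terms of interest and test country-by-characteristic interactions that include them, on 8 − 1 = 7 df per single-df term.
4. Optional: report a joint 7-df fixed-effect test of country beside the country-level variance, because that variance is imprecise with eight units.

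The cost is a few more model terms on data already being collected, and more tests to report.
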